## 1.0 INTRODUCTION

This Statistical Analysis Plan (SAP) for CTN-0099 ED-INNOVATION was prepared and developed by the Clinical Trials Network's (CTN) Data and Statistics Center (DSC) and the Lead Node (LN) according to version 5.0 of the protocol and describes all planned analyses for the primary, key secondary, and safety outcome measures. The CTN DSC will conduct analyses pertaining to the primary outcomes measures for the Ancillary and Randomized Clinical Trial (RCT) components, key secondary outcome measures for the RCT component of CTN-0099, all safety outcome measures, and all analyses for the primary outcome paper for the RCT component as discussed and agreed upon by the LN, DSC, and the Center for Clinical Trials Network (CCTN). The LN will be responsible for all other analyses, including all analyses for the Site Implementation (SI) component and the Electronic Health Records (EHR) Opioid-Related Phenotypes Component.

| Exhibit 1: Analysis Responsibilities                             |                       |                                 |
|-------------------------------------------------------------------------|-----------------------|---------------------------------|
| Content                                                          | Section Number | Responsible for Analysis |
| Participant Enrollment, Disposition, and Follow-up               | 4.0                   | DSC                             |
| Participant Baseline Characteristics                             | 5.0                   | DSC                             |
| Study Medication Adherence                                       | 6.0                   | DSC                             |
| Analyses of Primary Outcome Measure – Ancillary Component        | 7.1.2, 7.1.3          | DSC                             |
| Analyses of the Secondary Outcome Measures – Ancillary Component | 7.1.7                 | LN                              |
| Analyses of Primary Outcome Measure – RCT                        | 7.2.2, 7.2.3          | DSC*                            |
| Analyses of the Secondary Outcome Measures – RCT                 | 7.2.4                 | DSC/LN                          |
| Analyses of the Exploratory Outcome Measures                     | 7.2.6                 | LN                              |
|                                                                         |                       |                                 |
| Safety Outcomes                                                  | 8.0                   | DSC                             |
| Interim Analyses                                                 | 11.0                  | DSC                             |
| Data Quality                                                     | 12.0                  | DSC                             |

\* The DSC will analyze five key secondary measures from the RCT as noted in Section 7.2.4

## 2.0 SUMMARY OF STUDY DESIGN AND PROCEDURES

### 2.1 Study Objectives

Previous studies have demonstrated that emergency department (ED)-initiated sublingual buprenorphine (SL-BUP) with referral for ongoing opioid agonist treatment (OAT) is superior to referral alone or a facilitated referral for engaging ED patients in formal addiction treatment at 30 days (D'Onofrio *et al.*, 2015). Subsequent CTN ED buprenorphine (BUP) implementation studies (CTN-0069 and CTN-0079) have identified a variety of patient barriers including a lack of ED providers with DATA 2000 waivers to prescribe BUP; factors related to patients obtaining the medication in a timely manner such as outpatient pharmacy logistics; treatment availability (i.e.,

nearest location offering BUP and requirements of picture identification); and insurance issues (i.e., financial constraints if no insurance coverage and prior authorization requirements). Thus, innovative strategies such as the use of extended-release BUP (XR-BUP) may overcome these barriers in real world settings.

**SI component:** The primary objective of the SI component is to use implementation facilitation (IF) and training to achieve competence in ED-initiated XR-BUP and SL-BUP inductions in approximately 30 diverse ED sites. It is hypothesized that at least 80% (24) of the sites will achieve competence in both BUP induction procedures and meet all criteria for site initiation.

**RCT component:** The primary objective of the RCT component is to compare the effectiveness of XR-BUP and SL-BUP induction in approximately 2000 participants with untreated opioid use disorder (OUD) in the ED on the primary outcome of engagement in formal addiction treatment at 7 days. It is hypothesized that XR-BUP will result in more participants engaged in formal addiction treatment at 7 days. Secondary objectives are to examine the impact of XR-BUP induction on engagement in formal addiction treatment at 30 days and cost effectiveness compared to SL-BUP induction. Other secondary objectives include evaluating observation, monitoring, and follow-up outcomes.

**Ancillary component:** The primary objective of the Ancillary component is to assess opioid withdrawal symptoms over a 4-hour period among participants who have a Clinical Opiate Withdrawal Scale (COWS) (Wesson *et al.*, 2003) score less than 8 and receive ED-initiated XR-BUP. It is hypothesized that fewer than 20% of participants will experience a 5 or greater point increase in COWS score within 4 hours of XR-BUP administration, fewer than 10% of participants will transition to moderate withdrawal (COWS 13-24) within 4 hours of XR-BUP administration, and fewer than 10% of participants will experience clinician determined, and researcher adjudicated, precipitated withdrawal within 1 hour of XR-BUP administration.

**EHR Phenotypes component:** The primary objective of the EHR Phenotypes component is the development and validation of EHR opioid-related phenotypes for ED research. Specific focus will be on phenotypes encompassing the domain of opioid use (e.g., opioid withdrawal, opioid overdose, opioid use disorder) as they pertain to the overall study and other high priority phenotypes with dependent relationships (e.g., soft-tissue infections, chronic pain, mental health disorders). It is hypothesized that EHR phenotypes will accurately and automatically characterize key presentations of opioid-related illness.

## **2.2 Study Design and Procedures**

### **2.2.1 Study Design**

CTN-0099 is comprised of four components: Site Implementation (SI), Randomized Controlled Trial (RCT), Ancillary, and EHR phenotypes. In the SI component, components of IF will be utilized to enhance the adoption of ED-initiated buprenorphine at approximately 30 sites. Subsequently, an effectiveness comparison of two buprenorphine formulations (SL-BUP and XR-BUP) will be conducted, in an RCT, to engage ED participants with OUD in formal addiction treatment at 7 days. Site adoption and competency in ED-initiated buprenorphine will be assessed according to *a priori* initiation criteria across approximately 30 ED sites. Data serially extending from the SI/IF period through the RCT will be collected according to the RE-AIM (Reach, Effectiveness, Adoption, Implementation, Maintenance) framework to inform further implementation efforts. Concurrently, the Ancillary study will be conducted using a small case series designed to assess the safety of initiating XR-BUP in participants with a COWS < 8. The results of the Ancillary study will inform the larger RCT by potentially expanding the eligibility of participants with OUD who present with minimal to no symptoms of withdrawal. The final component, EHR Phenotypes, will develop and validate EHR phenotypes for participants with OUD.

**SI component:** In this component, previously developed implementation facilitation strategies and resources to train ED providers and staff will be used at approximately 30 diverse EDs in the induction of SL-BUP and XR-BUP, and ED buprenorphine protocols and procedures will be developed.

**Ancillary component:** The Ancillary component is an observational case series performed concurrent with the RCT component at approximately 4 ED sites with extensive experience in ED-initiated BUP and will collect quantitative and qualitative data on the use of XR-BUP in ED participants with low COWS scores ( $< 8$ ) for approximately 75 participants. It is a single arm trial among 75 participants to assess the safety of ED-initiated BUP in participants with low COWS scores on the basis of the percent of participants that experience a 5 or greater increase in COWS score, the percent that transition to moderate withdrawal (COWS 13-24), or the percent that experience clinician determined precipitated withdrawal. Participants who take part in the Ancillary component are similar to those in the RCT component, but with a lower COWS score required for entry. Results of the Ancillary component may allow modification to the RCT component by expanding eligibility criteria to include participants with a COWS  $< 8$  (see below\*).

The Ancillary component also contains a pre-study. In this pre-study, sites are provided a supply of XR-BUP for up to 5 participants with a COWS score of greater than or equal to 8. The purpose is to pilot the procedures prior to initiation of the Ancillary component. Data collected from this pre-study will not be included in the analysis of the Ancillary or RCT components.

After the initial 25 participants with COWS scores between 4 and 7 (inclusive) were enrolled in the Ancillary component, a DSMB Interim report was prepared for the DSMB. Based on the DSMB review that occurred on November 10, 2020, enrollment into the Ancillary component was expanded to include participants with COWS scores of less than 4 on November 18, 2020.

\*Based on results presented to the DSMB in April 2021 on the initial 75 patients, a desire to capture more information on patients with a COWS score of 0-3, and a DSMB recommendation in May 2021, recruitment for the Ancillary component was continued to include an additional 25 participants all with COWS  $< 4$ .

**RCT component:** The RCT component is a large pragmatic RCT using a Hybrid Type 1 Effectiveness-Implementation design (Curran *et al.*, 2012). Sites that satisfactorily complete the SI component will be activated on a rolling basis for the RCT after demonstrated implementation milestones have been met. The RCT is a parallel two-arm, open-label, pragmatic randomized trial in approximately 2,000 participants at approximately 25 sites to compare the effectiveness of SL-BUP induction to XR-BUP induction in the ED on engagement in formal addiction treatment at 7 days post-randomization. SL-BUP serves as the control for the trial. Participants who take part in the study are those who present to the ED with moderate to severe OUD and have urine toxicology positive for opioids, among other inclusion and exclusion criteria detailed in Section 2.3.

The RCT component may be expanded (see below\*\*) to include participants with COWS scores of less than 8 if certain *a priori* conditions on the primary outcome measures in the Ancillary component are met. If these *a priori* criteria are not met, the results will be reviewed with the Data and Safety Monitoring Board (DSMB) to get their recommendation as to which COWS scores less than 8 the RCT component may be expanded to include.

\*\*Based on results presented to the DSMB in April 2021 on the initial 75 patients in the Ancillary component, the inclusion criterion was updated to include participants with COWS  $\geq 4$ .

**EHR Phenotypes component:** In the EHR Phenotypes component, EHR phenotypes of opioid-related illnesses will be developed that accurately and automatically characterize patient conditions, enhance the ability to actively monitor and surveil, and better identify representative samples and patients potentially eligible for study inclusion, leading ultimately to an enhanced

inclusion and understanding of opioid-related conditions. At the primary Yale New Haven Health System sites, the phenotypes (rules- and machine learning-based) will be iteratively developed and internally validated. The rules-based phenotype will be mapped to a common data model and externally validated at four trial sites.

## **2.2.2 Study Assessments**

### **2.2.2.1 Ancillary Component**

A broad array of assessments will be conducted during the index ED visit, daily by telephone/text for 6 days, and in person on Day 7 (range Days 6-10) where the estimated day of ED discharge is Day 0.

Assessments completed at screening include, with electronic case report form (eCRF) in parentheses: ED Health Quiz (EHQ), Diagnostic and Statistical Manual of Mental Disorders (DSM)-5 (DSO), urine drug screen (UDS), COWS (COW), and patient eligibility summary (PES). Along with written informed consent, the following assessments are captured at enrollment: demographics (DEM and DM1), locator information (LOF), other substance use (OSU), TLFB (T99 and F99), health status (HST), and overdose events (ODE). Screening and enrollment assessments are completed at the index ED visit.

Assessments completed pre-injection include vital signs (VTR), assessments related to opioid withdrawal including COW and Objective Opiate Withdrawal Scale (OOW) (Handelsman *et al.*, 1987), pupillary diameter (PPD), craving/desire to use (CRV) (Kozlowski *et al.*, 1989), and bad drug effects (BDE) ([name] *et al.*, 2017). A numerical rating scale pain assessment (PAR) is completed immediately following the injection. The local tolerability scale (LTS) and PAR are completed 30 minutes post injection. Approximately every 30 minutes after the injection for 4 hours (240 minutes), the VTR, COW, OOW, and post injection medications (PIM) assessments are completed. At 240 minutes after the injection, the Adjective Rating Scale for Withdrawal (RSW) (Coloma-Carmona *et al.*, 2019), CRV, BDE, PAR, and LTS are completed.

Assessments completed by telephone/text on Days 1-6 include desire to use and daily substance use.

Assessments for the Day 7 visit include UDS, COW, ODE, an injection site assessment (ISR), satisfaction survey (S99), health services utilization (HS1, HS2, HSI, and HSO), engagement in treatment (ETP), and a study completion assessment (STC).

Ongoing and as needed during the study, adverse events (AEs), serious adverse events (SAEs), and protocol deviations are collected on the AD1, AD2, AD3, PDR, and PDV forms.

Forms relating to primary outcome measures include COW and the precipitated withdrawal assessment (PWD). The COW eCRF contains the COWS score at specific timepoints before and after the injection and the PWD eCRF is a simple yes/no questionnaire asking if, at approximately 240 minutes after the injection, a precipitated withdrawal occurred and at what time.

Refer to Section 9.11 of the protocol (version 5.0) for a full description of the assessments. Tables 3 and 4 in the protocol provide the schedule of study assessments.

### **2.2.2.2 RCT Component**

Aside from screening and enrollment, the only other study visits are 7-day and 30-day assessments. The participant baseline data will include a brief instrument assessing health status, healthcare utilization, overdose events, past 7-day alcohol and drug use including opioids using the Timeline Followback (TLFB) method (Sobel *et al.*, 1992), use of other substances, the HRQoL (health-related quality of life) measured using the Patient-Reported Outcomes Measurement Information System (PROMIS) (HealthMeasures, Accessed 8/15/2019), and other data necessary

to comprehensively measure costs from various stakeholder perspectives. Assessments collected at 30 days post study enrollment will be similar.

Refer to Section 8 in the protocol (version 4.0) for a full description of the assessments. Table 2 in the protocol provides the schedule of study assessments.

## **2.2.3 Study Treatments**

### **2.2.3.1 Ancillary Component**

Participants will receive a 24 mg dose of injectable CAM2038 in the ED under the supervision of the study clinician.

### **2.2.3.2 RCT Component**

Participants randomized to receive XR-BUP will receive one injection of CAM2038 24 mg in the ED on the day of the index visit. Participants randomized to the SL-BUP arm will receive 4 mg of SL-BUP for a COWS score of 8-12 (mild withdrawal). After 30-45 minutes if tolerated and no unanticipated adverse reactions occur, an additional 4 mg can be administered for a total of 8 mg in the ED. Participants presenting with moderate-severe withdrawal (COWS  $\geq$  13) will receive an initial dose of 8 mg SL-BUP. All participants will receive a buprenorphine prescription and instructions for additional BUP doses to allow for up to a dose of 12 mg if needed, and for 16 mg each subsequent day until their scheduled follow up appointment for ongoing MOUD (medication for OUD).

In April 2021, the protocol was modified to allow for patients with a COWS  $\geq$  4. No changes were made to XR-BUP induction process for these patients. The sublingual induction procedure was added such that for COWS 4-7, patients will be provided with a uniform set of instructions to guide unobserved (home) induction. They will be prescribed doses of SL-BUP to allow them to take dose up to 12mg in the 24 hours after discharge. All patients will also receive a buprenorphine prescription for 16mg each subsequent day until their scheduled follow up appointment for ongoing MOUD.

## **2.2.4 Treatment Randomization**

### **2.2.4.1 Ancillary Component**

No randomization is performed in the Ancillary component. All participants are to receive XR-BUP.

### **2.2.4.2 RCT Component**

Eligible participants will be randomized in a 1:1 ratio to XR-BUP or SL-BUP. Randomization is stratified by study site and insurance status at baseline (no insurance, public insurance, private insurance). The randomization process will be performed by computer by the DSC. A permuted block randomization procedure with random block sizes will be implemented to balance treatment assignments on site and insurance status.

## **2.2.5 Masking**

### **2.2.5.1 Ancillary Component**

As no randomization is performed in the Ancillary component, there is no masking.

### **2.2.5.2 RCT Component**

Fundamental differences in the two treatment arms are readily observed by research staff and this study is considered open-label or unmasked.

## **2.3 Eligibility Criteria for Selection of Study Population**

### **2.3.1 Ancillary Component**

#### **2.3.1.1 Inclusion Criteria**

All inclusion criteria below are as of protocol version 5.0.

All participants enrolled into the study must:

1. Be 18 years or older.
2. Treated in the ED during study screening hours.
3. Meet DSM-5 diagnostic criteria for moderate to severe opioid use disorder.
4. Have a COWS < 8 (after results from 75 participants were reviewed by DSMB, this criterion changed to COWS < 4).
5. Have a urine toxicology test that is positive for opioids (opiates, oxycodone, or buprenorphine). Patients with urines that are only positive for fentanyl on the point of care test strip will be eligible if their clinical history and physical exam are consistent with opioid use and they meet DSM-5 criteria for moderate to severe OUD.
6. Be able to speak English sufficiently to understand the study procedures and provide written informed consent to participate in the study.

#### **2.3.1.2 Exclusion Criteria**

All exclusion criteria below are as of protocol version 5.0.

All participants enrolled into the study must not:

1. Have a urine toxicology test that is positive for methadone.
2. Be pregnant as determined by human chorionic gonadotropin (hCG) testing at the index ED visit.
3. Have a medical or psychiatric condition that requires hospitalization at the index ED visit, prior to enrollment.
4. Be actively suicidal or severely cognitively impaired precluding informed consent.
5. Present from an extended care facility (e.g., skilled nursing facility).
6. Require continued prescription opioids for a pain condition.
7. Be a prisoner or in police custody at the time of index ED visit.
8. Be currently (anytime within the past 7 days) enrolled in formal addiction treatment, including by court order. Patients enrolled in formal addiction treatment but are not receiving MOUD are eligible.
9. Be unable to provide reliable locator information including 2 contact numbers in addition to their own.
10. Be unwilling to follow study procedures (e.g., unwilling to provide permission to answer daily assessments until day 7).
11. Have prior enrollment in the current study.

## **2.3.2 RCT Component**

### **2.3.2.1 Inclusion Criteria**

All inclusion criteria below are as of protocol version 5.0.

All participants enrolled into the study must:

1. Be 18 years or older.
2. Treated in the ED during study screening hours.
3. Meet DSM-5 diagnostic criteria for moderate to severe OUD.
4. Have a COWS score of  $\geq 4$  (changed from COWS  $\geq 8$  after review of the first 75 participants in the Ancillary component by the DSMB).
5. Have a urine toxicology test that is positive for opioids (opiates, oxycodone, buprenorphine). Patients with urines that are only positive for fentanyl will be eligible if their clinical history and physical exam are consistent with opioid use and they meet DSM-5 criteria for moderate to severe OUD.
6. Able to speak English sufficiently to understand the study procedures and provide written informed consent to participate in the study.

### **2.3.2.2 Exclusion Criteria**

All exclusion criteria below are as of protocol version 5.0.

All participants enrolled into the study must not:

1. Have urine toxicology test that is positive for methadone.
2. Be pregnant as determined by human chorionic gonadotropin (hCG) testing at the index ED visit.
3. Have a medical or psychiatric condition that requires hospitalization.
4. Opioid administration (excluding BUP) at the index ED visit, prior to enrollment, and COWS remains  $< 8$  during ED stay.
5. Be actively suicidal or severely cognitively impaired precluding informed consent.
6. Present from an extended care facility (e.g., skilled nursing facility).
7. Require continued prescription opioids for a pain condition.
8. Be a prisoner or in police custody at the time of index ED visit.
9. Be currently (anytime within the past 14 days) enrolled in formal addiction treatment, including by court order. Patients enrolled in formal addiction treatment who are not receiving MOUD are eligible.
10. Be unable to provide reliable locator information including 2 contact numbers in addition to their own.
11. Be unwilling to follow study procedures (e.g., unwilling to provide permission to contact referral provider/program or unavailable for the follow-up assessments).
12. Have prior enrollment in the current study component.

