## **8.3 Study Population**

### **8.3.1 Inclusion Criteria**

All patients enrolled into the study must:

1. Be 18 years or older
2. Treated in the ED during study screening hours
3. Meet DSM-5 diagnostic criteria for moderate to severe OUD

4. Have a COWS score of  $\geq 4$
5. Have a urine toxicology test that is positive for opioids (opiates, oxycodone, buprenorphine). Patients with urines that are only positive for fentanyl will be eligible if their clinical history and physical exam are consistent with opioid use and they meet DSM-5 criteria for moderate to severe OUD.
6. Able to speak English sufficiently to understand the study procedures and provide written informed consent to participate in the study. (Exception may be made if sites with large population of Spanish speaking patients are accepted for participation in the study and study materials are translated into Spanish. Translated study materials will be reviewed and approved by the IRB of record prior to use.)

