### 8.3.2 Exclusion Criteria

All patients enrolled into the study must not:

1. Have urine toxicology test that is positive for methadone
2. Be pregnant as determined by human chorionic gonadotropin (hCG) testing at the index ED visit
3. Have a medical or psychiatric condition that requires hospitalization.
4. Opioid administration (excluding BUP) at the index ED visit, prior to enrollment, and COWS remains  $< 4$  during ED stay
5. Be actively suicidal or severely cognitively impaired precluding informed consent
6. Present from an extended care facility (e.g., skilled nursing facility)
7. Require continued prescription opioids for a pain condition
8. Be a prisoner or in police custody at the time of index ED visit
9. Be currently (anytime within the past 14 days) enrolled in formal addiction treatment, including by court order. Patients enrolled in formal addiction treatment who are not receiving MOUD are eligible
10. Be unable to provide reliable locator information including 2 contact numbers in addition to their own
11. Be unwilling to follow study procedures (e.g., unwilling to provide permission to contact referral provider/program or unavailable for the follow-up assessments)
12. Have prior enrollment in the current study component

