### 8.9.5 Protocol Deviation Form

This form should be entered into the electronic data capture system whenever a protocol deviation occurs. This form will document a description of the deviation, how it occurred, the corrective action taken to resolve the specific deviation, as well as a description of the plan implemented to prevent future occurrences of similar deviations.

## 8.10 Potential Expansion of Eligibility Criteria to Include Cows < 8

If *a priori* criteria are met in the Ancillary Study described below in Section 9, in that fewer than 20% of those with a COWS score < 8 experience a 5 or greater point increase in COWS score within 4 hours of XR-BUP administration, there are <10% precipitated withdrawal events and <10% transition to moderate withdrawal (COWS 13-24), we will modify eligibility criteria for the

Effectiveness RCT component to allow patients with COWS < 8 to enter the RCT component. In the RCT component, those with a COWS < 8 will be randomized to XR-BUP vs. unobserved (home) induction. If these *a priori* criteria are not met, the data will be reviewed with the DSMB to get their recommendation as to which patients, if any, with a COWS < 8 should enter the RCT component.

If any patients in the Ancillary study component experience a 5 or greater point increase in COWS score within 4 hours of XR-BUP administration, precipitated withdrawal or patients that transition to moderate withdrawal (COWS 13-24), we will modify induction procedures or parameters (e.g., restrict to COWS > 4) based on discussion amongst the Lead PIs, the Ancillary component site PIs, Drs. [name] and [name], assigned NIDA Scientific Officer, and the assigned CTN Medical Monitor. This modification will be reviewed by the DSMB prior to implementation (see Ancillary study component below).

**Addendum:** On May 12, 2021, the DSMB reviewed the interim report from the initial 75 participants in the ancillary study and concurred that the study can proceed to expand the eligibility criteria for the remainder of the RCT component to include COWS scores of 4-7 (inclusive).

## 9.0 ANCILLARY STUDY COMPONENT: COWS < 8

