#### **3.2.1.2 Per Protocol (PP) Population**

The Per Protocol (PP) population will be a subset of the ITT population and exclude participants who did not receive study treatment as randomized such as refusing the injection, leaving the ED before medication could be administered, or opting for home induction in participants with COWS  $\geq 8$ . The PP population will also exclude participants who were enrolled and later found to be ineligible based on the inclusion and exclusion criteria. PP analyses will be performed according to the participant's actual treatment arm.

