## 7.2.2 Analysis of the Primary Outcome Measure

The primary outcome will be analyzed for the ITT population. Based on our primary aim and primary outcome, we hypothesize that the probability of treatment engagement at 7 days is greater among participants with OUD in the XR-BUP arm versus those in the SL-BUP arm, i.e., XR treatment is superior to SL.

The probability  $p_{XR}$  represents the probability of treatment engagement for a subject in the XR arm at Day 7, and the probability  $p_{SL}$  represents the probability of treatment engagement for a subject in the SL arm. Treatment superiority is operationally defined in terms of the odds ratio,

$$OR = [p_{XR} * (1 - p_{SL})] / [p_{SL} * (1 - p_{XR})]$$

Thus, the primary statistical hypotheses are:

$$H_0: OR = 1, \text{ i.e., XR is not superior to SL}$$

$$H_A: OR \neq 1, \text{ i.e., XR is different than SL}$$

An  $OR > 1$  and  $p\text{-value} < 0.05$  will indicate superiority of XR over SL with regard to the treatment engagement outcome.

The primary outcome, treatment engagement at 7 days (Y/N), will be assessed for the ITT population. Treatment engagement will also be assessed at 30 days. Treatment differences (XR vs. SL) for this dichotomous outcome will be examined using weighted GEE. The traditional GEE approach is valid under the strong assumption that missing data is missing completely at random

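### SAP RCT exclusion 4 uses a COWS threshold of 8 where the protocol uses 4, and the per-protocol definition does not say which text decides eligibility

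*Combined protocol and SAP*

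**What the plan says.** Protocol Section 8.3.2, exclusion 4, concerns patients given an opioid other than buprenorphine at the index ED visit before enrolment. It excludes them when "COWS remains $< 4$ during ED stay". SAP Section 2.3.2.2, exclusion 4, is worded the same apart from the number: "COWS remains $< 8$ during ED stay". The SAP introduces its list with the statement "All exclusion criteria below are as of protocol version 5.0".

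Both documents set RCT inclusion 4 at a COWS of at least 4. SAP Section 2.3.2.1 records that this was "changed from COWS $\geq 8$ after review of the first 75 participants in the Ancillary component by the DSMB". The addendum in protocol Section 8.10 reports the DSMB's agreement to admit scores 4-7 for the rest of the RCT.

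SAP Section 3.2.1.2 defines the per-protocol set. Besides removing people not treated as randomized, it states: "The PP population will also exclude participants who were enrolled and later found to be ineligible based on the inclusion and exclusion criteria". SAP Section 7.2.2 fixes the primary population: "The primary outcome will be analyzed for the ITT population". SAP Section 7.2.3 repeats the primary analysis in the per-protocol population as a supportive analysis.

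**The concern.** Inclusion 4 moved from 8 to 4, but exclusion 4 in the SAP still carries the old boundary. The two documents therefore disagree about one group: participants given a non-buprenorphine opioid before enrolment whose COWS never reaches 8 but is at least 4.

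This is more than a slip in background text, because the per-protocol definition turns on eligibility. The only RCT criteria printed in the SAP are those in Section 2.3.2, so a programmer working from the SAP alone would take the threshold of 8. One working from the protocol would take 4. They would build different per-protocol sets, and every participant on whom they differ would have a low COWS. SAP Section 7.2.3 also allows sensitivity analyses on the eligibility changes and runs the supportive analyses in both populations. Selective loss of low-COWS participants matters most there.

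**Working it through.** The mismatch rests on no stated figure, so the check is mainly a comparison of texts.

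**Step 1: compare the lists.** The other eleven RCT exclusions agree in substance between protocol 8.3.2 and SAP 2.3.2.2. Only the number in item 4 differs.

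**Step 2: compare the SAP with itself.** Three other places in the SAP treat COWS 4-7 as part of the trial population: inclusion 4 (2.3.2.1), the induction text for scores 4-7 (2.2.3.2) and the baseline category 4-7 (5.2). The per-protocol definition does so too, since it counts home induction as a departure only at COWS 8 or above.

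**Step 3: apply both rules.** A score that remains below k means that the highest COWS in the ED is below k. Take a participant given a non-buprenorphine opioid before enrolment, and use the highest score for inclusion as well:

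| Highest COWS in ED | Inclusion 4 (≥ 4) | Protocol exclusion 4 (< 4) | SAP exclusion 4 (< 8) | Do the documents agree? |
|---|---|---|---|---|
| 0-3 | not met | excluded | excluded | yes, ineligible |
| 4-7 | met | not excluded | excluded | **no** |
| 8 or more | met | not excluded | not excluded | yes, eligible |

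With a threshold of 4, exclusion 4 removes nobody who meets inclusion 4 on the same score. With 8, it removes everyone in the middle row.

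**Step 4: size.** The documents do not give the number in the middle row. To show a range, I first reproduced the design figure for a two-sample comparison of 45% with 53%, two-sided 0.05, 90% power:

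n = [1.960·√(2·0.49·0.51) + 1.282·√(0.45·0.55 + 0.53·0.47)]² / 0.08² = 819 per arm, or 844 with continuity correction.

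The plan states 850, which is within 3% of 844 − 844·0 = 844 (850/844 = 1.007). Also 1700/(1 − 0.15) = 2000. Power at 850 per arm, without continuity correction, is 91.0%.

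Next I assumed that a fraction f of both arms leaves the per-protocol set for this reason alone, so that n = 850·(1 − f):

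| Assumed f | Participants lost, both arms | Per-protocol power |
|---|---|---|
| 1% | 17 | 90.8% |
| 2% | 34 | 90.5% |
| 5% | 85 | 89.6% |
| 10% | 170 | 88.0% |

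These fractions are assumptions, not estimates. Even the largest costs about 3 percentage points of power in a supportive analysis. The issue is who leaves the set and whether its membership is defined, more than precision.

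**The case against.** The strongest reply is that nobody need be removed. The list in SAP 2.3.2.2 sits in a section summarizing the design, and the per-protocol definition does not cite it. Eligibility is decided at enrolment under the protocol and recorded on eligibility forms. A participant correctly enrolled under protocol exclusion 4 would not later be found ineligible by that process. This stands in part: removal follows only if the SAP list is the reference. But the definition names no reference, and that silence is itself part of the problem.

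It can also be said that the SAP's two items are not logically incompatible, since a patient at COWS 4-7 with no ED opioid passes both. That is true, but a stricter rule for opioid recipients appears nowhere in the protocol supplied.

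SAP Section 14.3 calls the RCT analyses a first draft, with version 4.0 to follow. That makes the correction easy; it does not remove the conflict.

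Three stronger readings are tempting and not supported:

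- **Deviation counts.** A reader might infer that these become wrong. Protocol Section 14.21 defines deviations against the protocol and has them recorded on a CRF, and SAP Section 12.2 tabulates what was reported. Nothing recalculates them from the SAP list.
- **Bias between arms.** A reader might infer this because SL-BUP participants at COWS 4-7 have home induction. The criterion concerns events before enrolment and applies to both arms alike, and the documents show no imbalance.
- **Transcription error.** The version number of the protocol supplied is not visible. If version 5.0 itself printed 8, the SAP is out of date rather than miscopied. The conflict with the protocol supplied remains either way.

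**Conclusion.** The conflict is real: SAP exclusion 4 disagrees with protocol exclusion 4 and is out of step with SAP inclusion 4. Its consequence is conditional. If the per-protocol set is built from the SAP list as printed, it loses participants given a non-buprenorphine opioid before enrolment whose COWS stays at 4-7 for the whole ED stay. The protocol supplied makes them eligible. A reader might infer that such removals are certain; they do not occur if the protocol or the eligibility forms decide.

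The number affected is unknown. It needs both an opioid dose before enrolment and a score that never reaches 8. The ITT primary analysis and the sample size do not change, and SAP Section 7.2.4 limits the secondary outcomes to ITT. The point should be settled before lock, because a choice about per-protocol membership made after outcomes are known would be hard to defend.

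**What to change.** Make two edits in SAP version 4.0, before RCT database lock:

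1. Reconcile exclusion 4 in SAP Section 2.3.2.2 with exclusion 4 in protocol Section 8.3.2, and check that the stated protocol version matches the list.
2. Add a sentence to SAP Section 3.2.1.2 saying that per-protocol eligibility is judged by the protocol version in force when each participant was enrolled. This also covers participants who entered before the COWS criterion changed.

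The cost is one number and one sentence. No new data are needed, and the primary analysis stays as it is.
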